### Evaluation and analysis plan

Mixed methods, including in-depth interviews and surveys, will be collected using clinical forms, completed by clients and providers. The evaluation and analysis plan are organized according to the following domains by aims: RE-AIM outcomes (Fidelity to MCCD), barriers and facilitators of implementation, and cost-effectiveness.

### Outcome evaluation and analysis for AIM 1 (Fidelity to MCCD)

#### Power analysis

We used the pwr package in R software to determine the sample size and estimate power to detect a small eta-squared effect size of 0.025 with an expected intra-class correlation coefficient (ICC) of 0.2. Our primary outcome analyses focus on the 12-month timepoint, we will enroll 10 providers per site resulting a total of 360 providers (180 CHS staff and 180 non-CHS staff) across 36 sites in order to achieve 80% power to detect the small effect size. We also enroll 18 clients per site per phase which results in a total of 648 clients over two phases. With client outcome, power calculations assume near-normal outcomes with a two-sided Type I error of 0.05, this design has 80% power to detect small effects (small Cohen’s d effect size of 0.14 for a 3 × 3 contingency table chi-square test, given 4 degrees of freedom [(3 intervention groups {UI, UI + ES, UI + ES + CELC} − 1)*(3 outcome levels of PHQ-9 score change from baseline to 6 months {positive change, no change, negative change} − 1)]).

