### Study site eligibility and recruitment

We are recruiting 36 community health stations (CHSs) from two provinces (Bac Giang and Phu Tho) that are located within a one-to two-hour drive from Hanoi capital. CHSs from each province will be randomly assigned into one of three intervention conditions with two implementation support phases: Phase 1—Active Implementation Support, and Phase 2—Sustainable Support (e.g., after supervision is withdrawn from the international training team and transitioned to the local supervision team). The recruitment process involves (1) identifying three potential districts per province based on recommendations from the provincial health department and psychiatric hospital, (2) conducting engagement meetings with three district-level health leaders to introduce the project and expectations, (3) conducting engagement meetings with CHS leaders to introduce the program, and (4) inviting interested CHS administrators to submit a form indicating interest in participating, as well as willingness to be randomized, and to complete a brief CHS assessment survey.

CHS selection criteria include having at least one physician/physician assistant, ≥ 5 CHS staff, ≥ 5 non-CHS staff including health collaborators/Village health workers (VHWs), serving a population of at least 5,000, and of which, ≥ 200 clients visit CHS monthly. We will score CHSs based on two main categories: (1) *site characteristics* (e.g., distance to district health centers and provincial psychiatric hospital, staff-to-client ratio, number of clients per month); and (2) *MH indicators* (e.g., implementing any MH programs, management and treatment for schizophrenia and epilepsy clients, accessibility to psychotropic medications). Given the total summary scores, CHSs will be classified as high- and low-performing sites. We will use Statistical Analysis Software (SAS) version 9.4 to randomly assign CHSs within a province into one of three conditions and the randomization process occurs within matched sites within district level, resulting in 6 UI, 6 ES, and 6 CELC. Each intervention arm will include 3 high performers and 3 low performers. Due to cost and staffing, we are implementing intervention at 18 CHSs in Bac Giang in the first year (2022) and will be continuing at 18 CHSs in Phu Tho in February, 2023.

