#### Provider selection

Based on power considerations, we will recruit 10 providers from each CHS and 360 across the study, including five primary care providers (usually physician assistants or nurses) from the CHS and five (usually VHWs) working with the CHS, totaling 180 CHS providers and 180 non-CHS staff. Providers will be recruited post-enrollment but pre-CHS randomization at each CHS.

We will use a repeated measure design to conduct online self-reported surveys with CHS and non-CHS providers at baseline (before the workshop, during the study enrollment meeting), 6-, 12-, and 24-month follow-up. All follow-up surveys will be distributed and collected by the research coordinator within a one-week period of each data collection time point. The survey will assess the following categories: socio-demographic characteristics (e.g., year of birth, gender, education, number of years working in health system), MH training, depression care attitude scale using the adapted Evidence-Based Practice Attitude Scale (EBPAS) [50], working environment using the Implementation Climate Scale (ICS) [51], CHS head’s leadership using the Implementation Leadership Scale (ILS) [52], depression care activities (e.g., frequency of depression screening and depression treatment offered) and skills, depression stigma [53] and depression knowledge quiz including 20 multiple-choices questions which covers all training topics.

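### The stated 80% provider-level power is not compatible with the plan's own ICC of 0.2; for an unadjusted comparison it is about one third

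*Protocol article*

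**What the plan says.** The protocol article, under Power analysis, states: "We used the pwr package in R software to determine the sample size and estimate power". The target is "to detect a small eta-squared effect size of 0.025 with an expected intra-class correlation coefficient (ICC) of 0.2". The primary analyses are placed at 12 months, and enrolment is described as follows: "we will enroll 10 providers per site resulting a total of 360 providers (180 CHS staff and 180 non-CHS staff) across 36 sites". The reason given for choosing that number is "in order to achieve 80% power to detect the small effect size". The Provider selection section relies on this calculation: on power grounds, "we will recruit 10 providers from each CHS and 360 across the study".

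The Abstract and the section on study site eligibility and recruitment make the CHS the randomised unit. Allocation within each province is described as "resulting in 6 UI, 6 ES, and 6 CELC", so two provinces give 12 CHSs and 120 providers per arm. For arm differences in the RE-AIM indicators, the RE-AIM outcomes section names an independent ANOVA or a Kruskal-Wallis test. The article gives no design effect, effective sample size or adjustment gain that would link an ICC of 0.2 to 80% power.

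**The concern.** An ICC of 0.2 with 10 people per cluster nearly triples the variance of an arm mean. A total of 360 is close to what an unclustered three-arm ANOVA needs for eta-squared 0.025, which suggests that the ICC is quoted beside the result but not reflected in it.

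The Study design section says the trial will mainly test effects on provider adoption and implementation quality, and this is the article's only power statement for provider outcomes. If true power is far below 80%, a null 12-month comparison of enhanced supervision or the learning collaborative with usual implementation would say little about small effects. A reader relying on the stated 80% could take it as evidence against them.

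**Working it through.** **Inputs from the protocol article**

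- Effect size: eta-squared 0.025 (Power analysis).
- ICC: "expected intra-class correlation coefficient (ICC) of 0.2" (Power analysis).
- Cluster size m = 10, with 36 CHSs and N = 360 (Power analysis).
- Three equal arms of 12 CHSs each (study site eligibility and recruitment).
- Alpha 0.05. The article states this for the client outcome ("power calculations assume near-normal outcomes with a two-sided Type I error of 0.05"); that it also applies to providers is an assumption.

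**Effect size.** f² = 0.025 / (1 − 0.025) = 0.02564, so f = 0.160.

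**Step 1: the plan's figure, ignoring clustering.** One-way ANOVA with 3 groups, noncentral F with df1 = 2 and df2 = 357:

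- λ = N × f² = 360 × 0.02564 = 9.23
- Power = 77.8%
- N needed for 80% = 379

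This does not give exactly 80% at 360, but it is within about 2 points.

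**Step 2: apply the stated ICC.**

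- Design effect = 1 + (m − 1) × ICC = 1 + 9 × 0.2 = 2.8
- Effective N = 360 / 2.8 = 128.6
- λ = 128.6 × 0.02564 = 3.30
- Power = 34.2% with df2 = effective N − 3
- Power = 32.3% with df2 = 36 − 3 = 33, the cluster-level degrees of freedom

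A simulation of an ANOVA on CHS means (12 per arm, 10 providers per CHS, ICC 0.2) gives about 32%.

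**Step 3: could a different number of providers per CHS rescue the claim?** As m grows without limit, the variance of a CHS mean falls only to the ICC, 0.2 in units of the total variance. Then λ = 36 × 0.02564 / 0.2 = 4.62, and power with 33 df is about 43%. For an unadjusted comparison, 36 CHSs, ICC 0.2, eta-squared 0.025 and 80% power cannot all hold, whatever the cluster size.

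**Step 4: sensitivity to the ICC** (36 × 10, eta-squared 0.025)

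| ICC | Design effect | Effective N | Power, 33 df | Power, effective-N df |
|---|---|---|---|---|
| 0.02 | 1.18 | 305 | 66% | 70% |
| 0.05 | 1.45 | 248 | 57% | 61% |
| 0.10 | 1.90 | 189 | 45% | 48% |
| 0.20 | 2.80 | 129 | 32% | 34% |

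**Step 5: what the design can detect.** Solving for 80% power at ICC 0.2 gives eta-squared 0.071 (effective-N df) to 0.076 (33 df). Relative to 0.025 this is a factor of 2.8 to 3.0. Conversely, holding eta-squared at 0.025 would take about 111 CHSs and 1,110 providers.

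**Step 6: other readings of the calculation**

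- Alpha 0.10 instead of 0.05, with clustering: about 45%.
- A 1-df linear contrast across arms, with clustering: 42%.
- Averaging 3 or 4 repeated measurements per provider, with clustering: 35–40%.
- The ICC read as a within-person correlation over 2 to 4 surveys, with no CHS clustering: 94% or more.

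None of these gives 80%.

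**The case against.** The strongest reply is that one third is the power of an unadjusted comparison at one time point, while the design has features that could raise it. Randomisation is within province and within matched sites at district level, with high and low performers balanced across arms. Providers are also surveyed at baseline. Under assumptions the article does not state:

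- Matching that removes half of the between-CHS variance would give about 46–48%; removing three quarters would give about 60–62%.
- Baseline adjustment with a correlation of 0.5, at both CHS and provider level, would give 42–44%. A correlation of 0.8 would give 74–77%, and 0.85 would give 85–88%.

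So 80% is reachable, but only with a very strong baseline correlation or a combination of gains. The article claims none of these for provider outcomes, and the only arm comparison it names for the RE-AIM indicators is ANOVA or Kruskal-Wallis. The objection therefore does not rescue the statement as written. It does mean that one third must be labelled as the unadjusted figure.

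Three further points stand. That the ICC was never applied is an inference, because the calculation is not shown and even the unclustered formula gives 78% rather than 80%. Alpha for the provider calculation is assumed. The reach of the problem is also limited: many RE-AIM indicators in Table 1 are measured on clients or from records, and the client survey has its own power statement. The outcomes affected are those measured on providers, such as self-reported adoption.

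**Conclusion.** The concern holds. At the plan's own ICC, cluster size and number of sites, power for eta-squared 0.025 is 32–34%, not 80%. The stated figure lies about 2 points from the unclustered result and more than 45 points from the clustered one, so the likely explanation is that clustering did not enter the calculation. The conclusion rests on a two-sided 5% level, equal arms, complete 12-month data and no covariate or matching adjustment. It does not depend on the exact ICC: at a quarter of the stated value, power is still only 57–61%. This needs correcting because the main design claim for provider outcomes overstates power by a factor of more than two.

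**What to change.** Keep the sample and restate the claim in the Power analysis section, for example:

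> With 36 CHSs and 10 providers per CHS, an ICC of 0.2 (design effect 2.8, effective sample size about 129) and a two-sided 5% level, an unadjusted three-arm comparison at 12 months has about 32–34% power for eta-squared 0.025 and 80% power for eta-squared of about 0.07–0.08.

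Remove the claim of 80% power for a small effect, and show power for ICCs from 0.05 to 0.20. If the provider analysis will adjust for baseline or for the matching, say so and give the resulting power under a stated correlation or a stated share of between-CHS variance removed.

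The cost is wording in one section. No sites or providers are added; the stated power becomes less favourable.

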## Methods

### Study design

This Type-II Hybrid Implementation-Effectiveness study [40] will primarily test implementation strategies on provider adoption and implementation quality. We will use a cluster RCT design to test the effectiveness of the implementation models on provider- and client-level outcomes with a mixed-methods approach. Specifically, this three-arm trial compares the three multi-component strategies for implementing depression care guidelines: (1) UI arm which includes basic depression care capacity workshops, limited technical assistance, and toolkits, 2) ES arm which includes all components of UI and additional structured clinical supervision from provincial and district supervisors, and 3) CELC arm which includes all components of ES, combined with the activation of a community-wide network of providers and stakeholders who are implementing continuous QI strategies (Fig. 1). The primary outcome is to compare the fidelity of MCCD on three implementation models using the RE-AIM framework [41], which will be assessed based on implementation outcomes (**R**each, **A**doption, **I**mplementation quality, and **M**aintenance) and provider and client-related outcomes (**E**ffectiveness) (Table 1). The secondary outcome is to assess factors associated with barriers and facilitators of quality implementation, which may serve as mechanisms for implementing additional supports for the ES and CELC arms. The tertiary outcome is to evaluate the incremental cost-effectiveness which quantifies the cost savings to policymakers when integrating various strategies for task-shifting depression care into primary care settings.

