**Implementation Quality**		
Adherence	Degree of fidelity to the content of the BA sessions	Supervision Ratings
Quality	General quality implementing the BA sessions	Supervision Ratings
Depression Care Competence	Depression care competence rated by supervisors	Provider Competency Assessment
Treatment Completion	# and % of clients with 4 or more sessions	Session Progress Note
Treatment Dropout	# and % of clients with 1 or less sessions	Session Progress Note
**Effectiveness**	Pre- and post-treatment differences; PHQ-9 Survey data	PHQ-9 Treatment Data and Survey Data
Client Improvement	50% reduction in PHQ-9 score	PHQ-9 – Session Scores (first and last)
Client Remission	Last PHQ-9 < 5	PHQ-9 – Session Score (last)
**Maintenance**	Independent implementation is considered an early sign of maintenance or penetration	Active Implementation Support; Transitional Support

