### Arm 1: usual implementation (UI)

#### Staff

All CHS staff will attend a series of hybrid depression care capacity training which includes a total of five weeks of online self-learning modules, four in-person workshops and five online Zoom-based webinars (totaling approximately 50 hours of hybrid training), implementation toolkits (e.g., BA manual, program implementation manual, clinical forms, workflow, clinical flow charts, health education materials), and limited technical support from national-level training team (e.g., initial program setup, observing depression screening and assessment) prior to the official rollout of the depression care program. All CHS staff will be trained to document service delivery using documentation tools, such as the screening log, screening and clinical intake assessment forms, session notes, and other clinical support forms. These forms will serve as the program’s administrative records. Additionally, non-CHS staff will attend a MH education and community outreach training which include two-week online learning on Moodle system and two-day in-person workshop. All non-CHS staff will be trained on promoting and educating MH in the community, screening for depression using the PHQ-4 as well as referring at-risk people and supporting care navigation to ensure successful linkages to CHSs.

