### Arm 2: enhanced Supervision (ES)

CHS providers will receive the same training and toolkits as those in the UI group, with an additional nine months of bi-weekly to monthly group supervision support from national, provincial, and district-level supervisors. Providers will receive three-hour biweekly in-person group supervision during the first three months of post-training project implementation. This is followed by monthly group supervision for the remaining 6 months of phase 1—Active Implementation Support. Clinical group supervision/consultation provided by provincial- and district-level health providers has three aims: (1) to support implementation activities and problem-solve barriers to implementation at the CHS; (2) to enhance CHS providers’ skills in providing BA by observing sessions and providing structured feedbacks (e.g., adherence and quality rating scale); (3) to assess CHS providers’ depression care competence every 6 months.

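### One 80% power figure on 360 providers is stated for the Aim 1 primary analyses, but at most 180 of them can be rated on the provider-level implementation-quality indicators

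*Protocol article*

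**What the plan says.** Study design states that the trial "will primarily test implementation strategies on provider adoption and implementation quality", and it describes the primary outcome as fidelity of the care program, assessed through RE-AIM.

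The Power analysis section, placed under the Aim 1 (fidelity) heading, assumes a "small eta-squared effect size of 0.025 with an expected intra-class correlation coefficient (ICC) of 0.2". It refers to the primary outcome analyses at 12 months and says "we will enroll 10 providers per site resulting a total of 360 providers (180 CHS staff and 180 non-CHS staff) across 36 sites", giving 80% power. It names no single provider outcome to which that figure belongs. Provider selection repeats the split of five CHS and five non-CHS staff per site and says that the number was set on power grounds.

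Table 1 lists five implementation-quality indicators. Three are rated on providers: adherence ("Degree of fidelity to the content of the BA sessions"), general quality of the BA sessions, and depression care competence. Adherence and quality come from supervision ratings, and competence from a supervisor's assessment. The other two, treatment completion and dropout, are counted on clients.

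On roles, the UI arm description says "All non-CHS staff will be trained on promoting and educating MH in the community, screening for depression using the PHQ-4", together with referral and care navigation. It lists no BA training for this group. The Toolkits section gives the BA manual to CHS providers. The ES section begins "CHS providers will receive the same training and toolkits as those in the UI group" and then adds group supervision, with BA session observation, structured rating and six-monthly competence assessment, all written for CHS providers. The CELC arm inherits these components.

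**The concern.** One sample size and one power figure stand for all the provider-level primary analyses, yet the outcomes they cover do not share a denominator. Self-reported adoption comes from the provider survey, which both staff groups complete, so 360 is right there. BA adherence, BA quality and competence need someone who delivers BA and is rated by a supervisor. On the described roles that is the CHS half of the sample at most.

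A reader of the power paragraph would take 80% to apply to implementation quality as well. If those comparisons show no difference, the result could be reported as an adequately powered null finding when the design never had that power for them.

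**Working it through.** **Inputs.** From Power analysis: eta-squared 0.025, ICC 0.2, 360 providers, 36 sites, 10 per site, half of them CHS staff. From the site recruitment section: 6 sites per arm in each of two provinces, so 12 per arm. From the RE-AIM outcomes section: an ANOVA across the three arms. Assumed: alpha 0.05, which the article states only for the client outcome, and the same eta-squared for the rated indicators.

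**Formula.** Three-arm one-way ANOVA, noncentral F:
- f² = 0.025 / (1 − 0.025) = 0.02564.
- Unclustered: noncentrality λ = N × f², with 2 and N − 3 df.
- Clustered: design effect DE = 1 + (m − 1) × 0.2 for m providers per site, λ = (N / DE) × f², with 2 and 33 df (36 sites − 3 arms).

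**The plan's own figure first.** With N = 360 and no clustering, λ = 360 × 0.02564 = 9.23 and power is 77.8%. About 379 providers would be needed for 80%. The stated figure is therefore approached only when the stated ICC is left out. With the ICC, DE = 1 + 9 × 0.2 = 2.8, effective N = 360 / 2.8 = 128.6, λ = 3.30, and power is 32.3%.

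**CHS providers only, N = 180 (5 per site).**
- No clustering: λ = 180 × 0.02564 = 4.62, power 46.4%.
- ICC 0.2: DE = 1 + 4 × 0.2 = 1.8, effective N = 180 / 1.8 = 100, λ = 2.56, power 25.8%.

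| Providers | No clustering | ICC 0.2 |
|---|---|---|
| 360 (10 per site) | 77.8% | 32.3% |
| 180 (5 per site) | 46.4% | 25.8% |
| Difference | 31.4 points | about 6 points |

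Taking effective N − 3 as the denominator df instead of 33 gives 34.2% and 27.2% in the ICC column, a gap of 7 points.

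**Detectable effect at 80% power.** Without clustering, eta-squared is 0.026 with 360 and 0.052 with 180. At ICC 0.2 with 33 df it is 0.076 and 0.096.

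**Where the shortfall arises.** With 360 providers, applying the ICC takes power from 77.8% to 32.3%, a loss of 45.5 points. Moving from 360 to 180 at that ICC takes a further 6 or so.

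**If only ES and CELC are rated.** Two arms of 12 sites with 5 CHS providers give 2 × 12 × 5 = 120 rated providers. The comparison then has two arms and no UI reference. At the same eta-squared, λ = 120 × 0.02564 = 3.08 with 1 and 118 df, and power is 41.3% unclustered. At ICC 0.2, effective N = 120 / 1.8 = 66.7, with 1 and 22 df, and power is 24.0%. This is a different hypothesis from the three-arm one, so these figures are not directly comparable with the table.

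**The case against.** The strongest reply is that the 80% was never stated for BA fidelity. The power paragraph names no indicator, all 360 providers answer the 12-month survey, and adoption comes from that survey, so 360 is correct for the outcome that the authors may have had in mind. This stands for adoption. It does not clear the paragraph, which sits under the fidelity aim and speaks of the primary outcome analyses in general, while Study design names implementation quality beside adoption.

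Second, that non-CHS staff do not deliver BA is inferred from their training and is not stated in words. The Discussion says that other community health workers can deliver the model, but it is describing the earlier program. The training and supervision sections of this trial point the other way. It remains an inference.

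Third, clustering is much the larger defect. That is correct. A reader might take the drop from 80% to 46% as the effect of the staff mix; at the plan's own ICC the mix costs about 6 points. Nor is the loss constant across ICC values. It shrinks as the ICC rises and vanishes at 1, where both designs have an effective N of 36 (360 / 10 and 180 / 5).

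Fourth, 180 may itself be too many, because structured supervision ratings are described only for ES and CELC. This stands, and it is why 180 is given as an upper bound.

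A reader might also infer that pooling the two staff groups on survey outcomes dilutes or biases the arm comparison, so that CHS staff should be the primary survey population. The article does not support this. It does not say how the effect divides between staff groups, and Table 2 records supervision and learning-collaborative time for non-CHS participants. Whole sites are randomised and providers are recruited beforehand, so the all-provider comparison is a legitimate estimand.

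**Conclusion.** The point holds in a limited form. The stated 80% is not available for the provider-rated implementation-quality indicators on any reading checked. With at most 180 CHS providers in three arms, power is about 46% if clustering is ignored and about 26% at ICC 0.2. The corresponding values for 360 are 78% and 32%.

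It would go too far to say that half of the primary test is affected. The article elsewhere defines the primary outcome as the whole RE-AIM set, adoption keeps its 360 respondents, and two of the five implementation-quality indicators are counted on clients. Three indicators are affected.

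The result rests on four assumptions: eta-squared 0.025 and alpha 0.05 apply to these indicators, non-CHS staff do not deliver BA, all five CHS staff per site are rated, and all three arms are rated. If the last fails, about 120 providers in two arms remain and there is no comparison with UI on those ratings.

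**What to change.** In the Power analysis section:

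1. Limit the 360-provider figure to survey outcomes that both staff groups answer, such as self-reported adoption, and restate its power with the ICC applied.
2. For BA adherence, BA quality and competence, state separately the number of providers rated, which arms are rated, and the power or detectable effect with the ICC applied. If all three arms are rated, that is 180 providers at 5 per site, with about 26% power at eta-squared 0.025, or 80% power for an eta-squared of about 0.096. If only ES and CELC are rated, say so and describe the comparison as a two-arm one.

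This changes the wording of one paragraph. No extra recruitment is needed. The cost is a less favourable stated power for a named primary target.

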**Methods:**

In this cluster-randomized controlled trial, CHSs will be randomly assigned to one of three implementation conditions: (1) Usual Implementation (UI), which consists of training workshops and toolkits; (2) Enhanced Supervision (ES), which includes UI combined with bi-weekly/monthly supervision; and (3) Community-Engaged Learning Collaborative (CELC), which includes all components of ES, combined with bi-monthly province-wide learning collaborative meetings, during which cross-site learning and continuous quality improvement (QI) strategies are implemented to achieve better implementation outcomes. The primary outcome will be measured based on the RE-AIM framework (Reach, Effectiveness, Adoption, Implementation quality, and Maintenance) using indicators on implementation, provider, and client factors. The secondary outcome examines factors associated with barriers and facilitators of quality implementation, while the tertiary outcome evaluates the incremental cost-effectiveness ratio of services provided in the ES and CELC conditions, relative to UI condition for depression care. A total of 1,296 clients receiving depression care at CHSs will be surveyed at baseline and 6-month follow-up to assess mental health and psychosocial outcomes (e.g., depression and anxiety severity, health function, quality of life). Additionally, 180 CHS staff and 180 non-CHS staff will complete pre- and post-training evaluation and surveys at baseline, 6, 12, and 24 months.

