#### Client outcomes

Clients identified with depression as part of routine depression screening at CHS will be recruited to participate in the client outcomes survey study across two implementation support phases. Eligible clients included those who are (1) new to the program, (2) aged 18–65, and (3) screened positive for depression using the PHQ-9 (score > 9). Those with a risk for severe mental illness (psychosis, mania, and substance abuse) will be excluded from the Client Study Cohort and referred to the provincial psychiatric hospital, per the stepped care model mentioned in the intervention description. Based on a depression screening rate of 20% and a research acceptance rate of 75% from our prior work [20], we expect CHS staff to screen 2,200 clients to consent 324 participants across each province for each Client Study Cohort. Across the total sample of 648 clients in each implementation phase. We will request permission from participants to link survey data to client administrative and clinical data.

The effectiveness on the client outcome will be measured based on the client’s improvement (defined as a 50% reduction in PHQ-9 score between the first and last BA session) and client’s remission (defined as the last PHQ-9 score less than 5). We will conduct an intent-to-treat analysis (e.g., those who are lost to follow-up are considered neither improved nor remised) in order to ensure the randomization process. A generalized linear mixed-effects model will be used for binary outcomes with a binominal family distribution and logit link. Exponentiating the fix-effect coefficients for treatment conditions will result in estimates of the odds ratio regarding the effect of treatment condition on depression symptomatology. These models will be adjusted for the clustering effects across multiple levels of hierarchical data structure (e.g., providers, clients) and the UI intervention will be used as a reference group.

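### The client total of 648 is one phase's cohort, not two, and the client model names one odds ratio per arm although ES support differs between the phases

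*Protocol article*

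**What the plan says.** **Client numbers.** The Power analysis section says: "We also enroll 18 clients per site per phase which results in a total of 648 clients over two phases". The Study site eligibility section says: "We are recruiting 36 community health stations (CHSs) from two provinces", with the allocation in each province "resulting in 6 UI, 6 ES, and 6 CELC". The Abstract says: "A total of 1,296 clients receiving depression care at CHSs will be surveyed at baseline and 6-month follow-up". The Client outcomes section expects 324 consenting clients per province for each cohort and gives 648 as the number in each phase. Trial status reports 324 clients interviewed in Phase 1, when 18 stations had been recruited.

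**ES by phase.** The Abstract defines the arm as "Enhanced Supervision (ES), which includes UI combined with bi-weekly/monthly supervision". The Arm 2 section sets out nine months of group supervision: three months biweekly, then "This is followed by monthly group supervision for the remaining 6 months of phase 1—Active Implementation Support". It describes nothing after that. The Study site eligibility section places Phase 2 "after supervision is withdrawn from the international training team and transitioned to the local supervision team".

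**Client model.** The Client outcomes section recruits clients in both phases. It specifies a logistic mixed model with UI as reference and an adjustment for clustering: "Exponentiating the fix-effect coefficients for treatment conditions will result in estimates of the odds ratio regarding the effect of treatment condition on depression symptomatology". It names no phase term, no arm-by-phase term and no restriction to one phase.

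**Maintenance.** Table 1 lists Maintenance apart from Effectiveness and links it to the active and transitional support periods. The Aim 3 section measures maintenance at 24 months, and includes effectiveness in it.

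**The concern.** There are two linked faults. First, the total in the power statement does not follow from its own inputs, so a reader cannot tell whether the claimed power belongs to one phase's clients or to all of them.

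Second, the client effect has no stated phase. ES is delivered on its described schedule in Phase 1 and under a different supervision arrangement in Phase 2, and new clients enter in each. One odds ratio per arm, fitted to everyone, is an average of two contrasts. It answers neither the effectiveness question (what ES does while active support runs) nor the maintenance question (what remains after the transition), although the article treats these as separate RE-AIM domains. If part of the effect is lost in Phase 2, the average lies below the Phase 1 effect and does not show the loss. Leaving the phase open also allows a choice between pooled and per-phase results after the data are seen.

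**Working it through.** **1. The total.** Inputs: 18 clients per site per phase (Power analysis) and 36 sites (Study site eligibility).
- One phase: 18 × 36 = 648.
- Two phases: 18 × 36 × 2 = 1,296.

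The other sections agree: 324 per province × 2 provinces = 648 per cohort (Client outcomes); 324 / 18 stations = 18 per station in Phase 1 (Trial status); 1,296 overall (Abstract). Only the power sentence attaches 648 to both phases.

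**2. The power figure.** Inputs from the Power analysis section: 3 × 3 chi-square test, 4 df, two-sided alpha 0.05, 80% power, effect 0.14. The article calls the effect Cohen's d; for this test the measure is Cohen's w. Power is the upper tail of a noncentral chi-square with noncentrality N × w².

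| N | detectable w at 80% power | power at w = 0.14 |
|---|---|---|
| 648 | 0.136 | 82.7% |
| 1,296 | 0.096 | 99.0% |

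At w = 0.14 exactly, 80% power needs N = 609. The stated 0.14 is 0.136 rounded, so the calculation was done on 648 clients, which is one phase. It contains no clustering allowance.

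**3. Share of ES clients in Phase 2.** ES sites: 6 per province × 2 = 12. ES clients per phase: 12 × 18 = 216. Phase 2 share: 216 / 432 = 50%.

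**4. What a single odds ratio averages.** Let f be the share of the Phase 1 effect that persists in Phase 2. The article gives no f, so this is an assumption. With equal cohorts the pooled effect is about (1 + f)/2 of the Phase 1 effect: 1 at f = 1, 0.75 at f = 0.5, and 0.5 at f = 0.

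On the plan's own independent-client method, with Phase 1 w = 0.14 and all arm effects scaled by f in Phase 2:

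| f | pooled power, N = 1,296 |
|---|---|
| 1 | 99% |
| 0.75 | 96% |
| 0.5 | 87% |
| 0.25 | 71% |
| 0 | 50% |

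Phase 1 alone (N = 648) has 83%.

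**5. Standard-error cost of separating the phases.** The variance of a site mean is proportional to (1 + (m − 1) × ICC)/m, with m = 18 for one phase and m = 36 for both. The ICC of 0.2 in the Power analysis section stands with the eta-squared calculation and no client ICC is given, so a range is shown. The formula takes the site effect as fully shared across phases and is an approximation for a logistic model.

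| ICC | one phase | both phases | SE ratio | Phase 1 contrast stronger if f is below |
|---|---|---|---|---|
| 0.2 | 4.40/18 = 0.2444 | 8.00/36 = 0.2222 | 1.05 | 0.91 |
| 0.05 | 1.85/18 = 0.1028 | 2.75/36 = 0.0764 | 1.16 | 0.72 |
| 0.01 | 1.17/18 = 0.0650 | 1.35/36 = 0.0375 | 1.32 | 0.52 |
| 0 | 1/18 = 0.0556 | 1/36 = 0.0278 | 1.41 | 0.41 |

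The last column solves (1 + f)/2 = 1/(SE ratio).

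**The case against.** The best defence is that the article never says the phases are pooled. The Client outcomes section speaks of separate cohorts of 648, which fits an analysis by cohort, and a condensed article may leave a phase term to the full analysis plan. Maintenance is a domain of its own, so the authors evidently mean to look at it. This stands in part: pooling is implied, not declared. But the article does fix the model's family, link, fixed effects, reference arm, clustering and treatment of dropouts, directly after saying that clients come from both phases, and its power sentence speaks of a total over two phases. Someone following the text would fit one arm effect.

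Three stronger readings are tempting, and the documents do not support them.
- A reader might infer that ES supervision stops after Phase 1, so that half of the ES clients receive no ES. The Study site eligibility section says that supervision is handed to a local team, while the Arm 2 section is silent beyond month nine. Phase 2 clients also attend stations whose providers have already been supervised for nine months.
- A reader might infer that the trial was sized on 648 clients spread over both phases, so that dilution would act on that number. By steps 1 and 2, 648 is one phase, and a pooled analysis would have 1,296.
- A reader might infer that pooling must lose power. With independent clients and N = 1,296 it gains power over Phase 1 alone unless f is below about 0.41.

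**Conclusion.** The point holds in two parts. The total in the power sentence is wrong by a factor of two: 648 is one phase and 1,296 is both. The claim of 80% power at 0.14 belongs to one phase's cohort. This is firm arithmetic, supported by three other sections.

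The client model, as written, gives one odds ratio per arm for two cohorts treated under different supervision arrangements, half of the ES clients being in each. The result mixes effectiveness with maintenance. This rests on reading the model text as it stands, because pooling is not expressly stated. The size of any dilution cannot be given: it depends on the effect that persists in Phase 2 and on a client ICC, and the article states neither. The main harm is an unclear estimand; a loss of power is only possible.

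**What to change.** 1. In Power analysis, change the total to 648 clients per phase, 1,296 in all. State that the power claim applies to one phase's cohort and carries no clustering allowance.
2. In Client outcomes, add phase and arm-by-phase terms to the mixed model. Report the Phase 1 arm contrasts as effectiveness and the Phase 2 contrasts as maintenance, in place of one averaged odds ratio.
3. Reconcile the Study site eligibility and Arm 2 sections on what supervision ES sites receive in Phase 2.

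The cost is wording and model specification, with no new data. The downside is precision: each contrast has a standard error larger than a pooled one by about 5% at ICC 0.2, 16% at 0.05, 32% at 0.01 and 41% with no clustering. If site effects are only partly shared between phases, Phase 2 clients would add more to a pooled estimate, and the loss at a given ICC would be somewhat greater.
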